### Study design

This is a prospective non-randomized controlled trial. It is a two (group: intervention and control) by three (time: pre-treatment, 5 weeks, 6 months) repeated measures factorial design. The overall study design is illustrated in Fig. 1 and Table 1. In T0 sociodemographic data, medication, and use of previous psychotherapeutic inpatient or outpatient treatments, as well as data on health behavior (e.g. smoking, alcohol consumption, etc.) of the patients will be collected. Participants in the intervention group will complete a comprehensive web-based questionnaire battery at three time points: at the time of admission to the hospital setting (T0), at the end of inpatient treatment five weeks later (T1), and 6 months after discharge from the hospital setting (T2). The control group will accomplish the questionnaire within a time frame of around 6 months after presentation at the Post-COVID Center of the Universitätsklinikum Erlangen (T0), five weeks after T0 (T1), and 6 months after T0 (T2). The questionnaires at T0, T1, and T2 will be made available web-based via a link and a password. Participants who drop out of the intervention or control group will be reported in the final results. Before participation, written informed consent must be given. A schematic overview of the trial flow is given in Fig. 1. The instruments used at each time point are displayed in Table 1.

**Table 1 Tab1:** Overview of the assessment schedule for both groups

Measures	Assessment time points		
	Baseline (T0)	5 weeks later (T1)	6-month follow-up (T2)
Sociodemographic variables	X		
Health behavior	X	X	X
Use of PASC-specific treatments		X**	X
Use of PASC-specific outpatient or inpatient psychotherapeutic treatment	X	X**	X

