#### Data collection, data management, and data storage

Study data will be collected using Heartbeat Medical [68] and REDCap (Research Electronic Data Capture) [69, 70]. Data collection will take place within the clinic and will comply with the legal data protection conditions of the EU GDPR (European Union General Data Protection Regulation). The links for the questionnaires will be personalized, with a password sent by post to activate the link. To obtain the most complete data possible, patients are reminded twice to complete the questionnaires. Data will only be stored and processed in encrypted form. Each participant will be given a research number, so it will not be possible for outsiders to link the data to the individual. Only those responsible for the study, who are bound by medical confidentiality, will have access to a list of personal data and corresponding research numbers. This list will be kept under lock and key. The data will be published anonymously.

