#### Sample size calculation and statistical methods

Sample size calculation was performed with G*Power Version 3.1.9.7 [71, 72]. The sample size calculation is based on testing the primary hypothesis that inpatient psychosomatic treatment leads to a significantly lower mean PCS Score across the first two follow-up assessments (T1 and T2) as compared to treatment as usual. Because of the novelty of PASC, data on our primary outcome, the PCS Score, were not available in this population over different time points. Therefore, we assumed a conservative correlation of 0.5 among repeated measurements and a medium effect size. Based on a medium effect size (f = 0.25) and a power of 85%, a sample size of 98 participants is required, with 49 participants per group. Assuming a conservative dropout of 20%, we will randomize 118 participants, 58 for each condition.

We will perform standard techniques of data preparation with tests of normality and homogeneity and with imputation of missing data in the case of dropouts. Furthermore, we will conduct different descriptive analyses of sociodemographic and medical data. The primary statistical analyses will be a two-way mixed-design Analysis of Variance (ANOVA) with the independent variables being condition (treatment vs. treatment as usual) and time (T0, T1) and condition by time interaction as fixed effects as well as repeated measures ANOVA for the follow-up measurement with repeated measurements. Additionally, we will perform regression analyses to identify potential predictors of treatment outcomes. In all analyses, two-sided p values of < 0.05 are considered to indicate statistical significance. All analyses will be conducted using the statistical software SPSS.

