#### Ethical aspects

We do not believe the trial raises any ethical concerns. We are not aware of any specific risks or disadvantages that may affect patients during the trial, and we do not expect any specific adverse or serious adverse events. Any unexpected adverse or serious adverse events will be documented. During the trial, patients will have access to medical advice or face-to-face contact with a member of the study team (psychologist or physician) at any time, if needed. Side effects of evidence-based psychotherapies are fortunately quite rare. However, potential adverse effects may include lack of treatment response, the emergence of new symptoms, worsening of existing symptoms, strains in the therapist-patient relationship, challenges or changes in work, family, or other social relationships, stigmatization, and the development of a pathological dependence on the therapist [73–75]. In the event of adverse effects, the psychotherapist, physician, or therapist, possibly in consultation with supervisors, will assess the need for further treatment. To prevent adverse events, several measures are implemented, including (i) a training program to raise awareness of adverse events, (ii) special training for physicians, psychologists, and other therapists for the treatment of PASC, and (iii) supervision of psychotherapists, physicians, and other therapists.

The Ethics Committee of the Medical Faculty of Friedrich-Alexander Universität Erlangen-Nürnberg (FAU) has approved the study (22–443_1-B). Written informed consent is required for all patients to participate and will be obtained after proof of verbal and written information and before group allocation. All participating patients can withdraw at any time without disadvantage. In the event of non-consent to participation in the study or withdrawal, patients will not suffer any disadvantages in terms of diagnostics, psychosomatic, or further treatment. Patients will be informed of this in detail in advance.

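### Intervention T1 and T2 hang on the end of treatment and discharge, control T1 and T2 on T0, so an early leaver's primary assessment has no clear date and T2 shifts with the date of leaving

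*Protocol article*

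**What the plan says.** The Study design section describes a "two (group: intervention and control) by three (time: pre-treatment, 5 weeks, 6 months) repeated measures factorial design". It then gives each group its own visit rule. The intervention group is assessed on admission (T0), then "at the end of inpatient treatment five weeks later (T1), and 6 months after discharge from the hospital setting (T2". The control group is assessed at T0, then "five weeks after T0 (T1), and 6 months after T0 (T2". The Outcomes section places the primary outcome, the PCS Score, at T1 and describes that point as the end of treatment. Table 1, which covers both groups, heads the T1 column as five weeks after baseline.

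On collection, the same section says: "The questionnaires at T0, T1, and T2 will be made available web-based via a link and a password". The data collection section adds: "To obtain the most complete data possible, patients are reminded twice to complete the questionnaires".

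On patients who leave, the Study design section says: "Participants who drop out of the intervention or control group will be reported in the final results". The statistical methods section provides for data preparation "with imputation of missing data in the case of dropouts" and names no imputation method. The Ethical aspects section lists among possible adverse effects "lack of treatment response, the emergence of new symptoms, worsening of existing symptoms".

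**The concern.** For a patient who stays the full five weeks, the two descriptions of T1 (end of treatment, five weeks after admission) name the same day. For a patient who leaves early they do not, and the text does not say which governs. This affects the primary endpoint. T2 is not ambiguous, but in the intervention group it depends on the discharge date, so the length of follow-up varies with how the stay went. In the control group it does not vary. Even among completers, the visit labelled six months lies about five weeks later than the control visit it is compared with.

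A second, weaker issue follows. The article uses one notion of dropout and does not distinguish a patient who stops inpatient treatment from one who leaves the study. Worsening is a plausible reason for stopping. If early leavers were classed as dropouts and their values imputed, that worsening could go unmeasured.

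**Working it through.** **1. T1 for an early leaver.** Take discharge at week 2 as an example.
- Anchor "end of treatment" is replaced here by its date: week 2 after T0.
- Anchor by elapsed time: week 5 after T0.
- Difference: 5 − 2 = 3 weeks. For a completer it is 5 − 5 = 0.

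**2. T2 measured from T0.** Six months is about 26.1 weeks.

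| Patient | Rule in the article | Weeks after T0 |
|---|---|---|
| Control | 6 months after T0 | 26.1 |
| Intervention, leaves at week 2 | 6 months after discharge | 2 + 26.1 = 28.1 |
| Intervention, completes | 6 months after discharge | 5 + 26.1 = 31.1 |

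Completers are therefore assessed 31.1 − 26.1 = 5 weeks later than controls, and a week-2 leaver 28.1 − 26.1 = 2 weeks later. This follows from the text with no assumption beyond the example discharge date.

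**3. The planned effect, as a yardstick.** The sample size section gives f = 0.25, correlation 0.5, two-sided alpha 0.05, power 85% and N = 98. The repeated-measures ANOVA for a between-group factor with m = 3 measurements has noncentrality f²·N·m / (1 + (m − 1)ρ) = 0.0625 × 98 × 3 / (1 + 2 × 0.5) = 9.19 on 1 and 96 degrees of freedom. Its power is 0.851, so 98 reproduces. With two equal groups, f = 0.25 corresponds to a difference of 2 × 0.25 = 0.5 SD.

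**4. Illustration of the imputation issue.** None of these inputs is in the article. Let a share q of the intervention group leave early, be w SD worse than completers, return no questionnaire, and be imputed at the completers' mean. The intervention mean is then too favourable by q × w.
- q = 0.05, w = 0.5: 0.025 SD, or 0.025 / 0.5 = 5% of the planned effect (0.05 × 58 = 2.9 patients).
- q = 0.20, w = 0.5: 0.10 SD, or 0.10 / 0.5 = 20% of the planned effect (0.20 × 58 = 11.6 patients).
- Early leavers who return their questionnaires contribute no such bias, whatever q is.

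The calculation leaves out any bias from imputing control dropouts, which could offset this.

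**The case against.** The strongest reply is that the timing is mostly clear and the rest is detail an article need not carry. The design factor and the Table 1 heading both put T1 at five weeks, which is the natural reading. The dropout sentence covers both groups, and controls have no study treatment to stop, so it most naturally means leaving the study. Questionnaires are completed remotely with two reminders, and nothing in the article ends this at early discharge. Imputation is provided for missing data, and nothing says that returned answers are discarded. Harm has other channels: weekly medical consultations, an examination at the end of treatment, and documentation of unexpected adverse events. A policy for patients who stop treatment, and the imputation method, commonly sit in the full protocol or the analysis plan.

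Most of this stands. A reader might infer that patients who stop because they worsen are not followed and that their harm is replaced by an imputed value. The article states neither. A reader might also work out a 25% overstatement: if 20% gain nothing, the true effect is 0.80 × 0.5 = 0.40 SD, against 0.50 SD reported, and 0.50 / 0.40 = 1.25. That treats the whole 20% dropout allowance, which covers both groups and all reasons, as early stoppers who supply no data and are imputed as completers. The documents support none of these steps, and the direction of any net bias is not established either.

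The reply does not remove the anchors themselves. They are stated rules, so this part is not a matter of omission. The five-week heading conflicts with an end-of-treatment anchor whenever a stay is cut short, and the Outcomes section repeats the treatment-based description for the primary outcome.

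**Conclusion.** The point holds as a defect in the stated visit schedule. The intervention group's visits depend on treatment events and the control group's on T0. For early leavers the date of the primary assessment is ambiguous (by three weeks in the week-2 example), and T2 varies from about 28 to about 31 weeks after T0, against about 26 in controls. These figures rest only on the article's wording and the example discharge date.

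That worsening could be masked is conditional: it requires early leavers to be handled as dropouts and imputed, which the article does not say. The 0.025 to 0.10 SD range shows what would follow under the stated assumptions and is not an estimate for this trial. The missing policy for early leavers and the unnamed imputation method would not, by themselves, be a finding against an article. The correction is worth making because it replaces a stated rule with a better one and needs only a change of wording.

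**What to change.** Define T1 as five weeks after T0 and T2 as the same fixed interval after T0 in both groups, whatever the length of stay, and align the Study design and Outcomes sections and Table 1 with that definition. State that patients who stop inpatient treatment still receive the T1 and T2 links and both reminders, that the values they return are analysed, and that imputation applies only where a questionnaire was not returned.

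The cost is wording: the links and reminders already exist. There are two downsides. If the common interval is six months, T2 for completers falls about five weeks sooner after discharge, so it is a shorter test of how long the benefit lasts. The reported effect may also be slightly less favourable once early leavers' own values are used. Some early leavers will still not respond, and imputation remains necessary for them.

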**Methods and analysis:**

This study presents a non-randomized controlled trial aimed at evaluating the effectiveness of a five-week multimodal inpatient psychosomatic treatment program for individuals experiencing PASC symptoms and comorbid mental illness. A total of 118 patients presented at the Post-COVID Center at the Universitätsklinikum Erlangen will be assigned to the intervention group receiving inpatient psychosomatic treatment or the control group receiving treatment as usual. The inclusion criteria for the intervention group are a diagnosis of PASC and at least one condition of mental distress and problems with coping with illness. The primary objective of the intervention is to reduce mental ailments, including depression and anxiety, as well as neurocognitive deficits, and to address PASC symptoms such as fatigue and pain. The core elements of the treatment are psychotherapy in individual and group settings, medical treatment, neurocognitive training, and physical therapy, adapted to the individual’s capacity and oriented towards the concept of pacing. After enrollment, participants will undergo a 6-month follow-up to assess long-term results and the sustainability of the intervention effects.

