### Primary hypothesis

We expect the intervention to be superior to treatment as usual (TAU) regarding a significantly lower mean of PASC symptoms measured by the Post-COVID Syndrome Scale (PCS Score) post-treatment and at 6 months follow-up.

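### T2 is counted from discharge in the intervention group but from T0 in the control group, so the follow-up comparison carries a five-week offset in elapsed time; the T1 primary comparison is not affected.

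*Protocol article*

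**What the plan says.** The Study design section of the protocol article defines the time points separately for each group.

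- Intervention: T0 is "at the time of admission to the hospital setting (T0"), T1 is "at the end of inpatient treatment five weeks later (T1"), and T2 is "6 months after discharge from the hospital setting (T2").
- Control: T0 is a questionnaire completed "within a time frame of around 6 months after presentation at the Post-COVID Center", and the later assessments are "five weeks after T0 (T1), and 6 months after T0 (T2").

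The same section describes the design as two groups by three times and gives one set of times for both groups. Table 1 likewise has a single T2 column for both groups.

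T2 carries weight in the plan. The Primary hypothesis section expects superiority on the PCS Score "post-treatment and at 6 months follow-up". The section on sample size and statistical methods bases the sample size on the mean PCS Score over T1 and T2, and plans a repeated measures ANOVA for the follow-up. However, the Primary outcome section names T1, and the primary ANOVA uses T0 and T1 only.

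**The concern.** The two groups reach T1 at the same distance from T0 and then diverge, because one T2 clock starts at discharge and the other at T0. A model that treats T2 as one level of time compares intervention patients at a later point with control patients at an earlier one. Any change in symptoms over those extra five weeks, whatever its cause, is then read as part of the group difference. Every questionnaire outcome that Table 1 places at T2 in both groups has the same offset.

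The problem is systematic and does not shrink with more patients. Nor can the analysis easily remove it. If the schedule is kept, days since T0 at T2 are almost fully determined by group, so an adjustment for elapsed time would be nearly collinear with the treatment effect and would rest on an assumed course. At stake is the follow-up claim, in a comparison that the article already acknowledges to be self-selected.

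**Working it through.** **Timing.** All inputs come from the Study design section, apart from the convention that six months = 365.25/2 = 182.6 days. Five weeks = 35 days.

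| Interval | Intervention | Control | Difference |
|---|---|---|---|
| T0 to T1 | 35 days | 35 days | 0 |
| T0 to T2 | 35 + 182.6 = 217.6 days (31.1 weeks) | 182.6 days (26.1 weeks) | 35 days |
| T1 to T2 | 182.6 days (26.1 weeks) | 182.6 − 35 = 147.6 days (21.1 weeks) | 35 days |

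Relative offset: 35 / 182.6 = 0.192, about 19% of the control group's follow-up. This assumes a full five-week stay; an earlier or later discharge changes it.

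**Possible size.** The article gives no course of the PCS Score over time, so a trend must be assumed. With a linear change of *c* per six months in both groups, the shift in the T2 group difference is *c* × 35 / 182.6 = 0.192 *c*.

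- *c* = 0: shift 0.
- *c* = 0.25 SD: 0.192 × 0.25 = 0.048 SD.
- *c* = 0.5 SD: 0.192 × 0.5 = 0.096 SD.
- In PCS points (scale 0 to 59), *c* = 1, 2 or 5 gives 0.19, 0.38 or 0.96 points.

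The sample size rests on the mean over T1 and T2. T1 has no offset, so the shift on that mean is half: 0 to 0.096 / 2 = 0.048 SD.

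**Direction.** If symptoms fade, the extra five weeks favour the intervention group. If they worsen, the sign reverses. A waning treatment effect also works against the intervention: its patients are seen 26.1 weeks after the end of treatment, not the 21.1 weeks that the control schedule would give.

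**Sample size.** The stated 98 participants are reproduced by the between-factors test of a repeated measures ANOVA with f = 0.25, correlation 0.5, two-sided alpha 0.05 and three measurements (the number of measurements is not stated; three follows the two-by-three design):

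λ = N f² m / (1 + (m − 1)ρ) = 98 × 0.0625 × 3 / (1 + 2 × 0.5) = 9.19, with 1 and 96 degrees of freedom, giving power 0.851.

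The date of an assessment does not enter this formula, so aligning T2 leaves the requirement at 98.

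**The case against.** The strongest reply is that the main result is not at risk. The named primary outcome is at T1, the primary ANOVA covers T0 and T1, and both groups have T1 five weeks after T0. This stands. A reader might infer that the whole primary comparison is biased; the document does not support that. T2 enters the primary claim only through the wording of the hypothesis and the basis of the sample size.

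Second, a reader might set 0.05 to 0.10 SD against d = 0.5 (the equivalent of f = 0.25) and report a bias of 10 to 19% of the planned effect in favour of the intervention. That does not hold. The planned effect refers to the T1/T2 mean, on which the same shift is half as large. The trend is assumed, zero is possible, and the sign is open. The Introduction itself reports that depressive and anxiety symptoms can last for a long time.

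Third, the abstract's "After enrollment, participants will undergo a 6-month follow-up" might be read as contradicting the intervention schedule. It gives the length of a follow-up and does not clearly fix its starting point. The T2 label in Table 1 is also compatible with either anchor.

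Fourth, T0 is itself anchored differently in the two groups (admission versus time since presentation), so aligning T2 does not put patients at the same point of their illness. This is true, but it is a separate matter and no reason to keep a further avoidable difference.

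Fig. 1 is not reproduced in the text at hand. Nothing in the text that is available reconciles the two anchors.

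**Conclusion.** The inconsistency is real and confined to T2; it should be fixed. Taken literally, the schedule puts T2 about 35 days (19%) later after T0 in the intervention group, provided that the stay lasts the planned five weeks. Elapsed time is therefore confounded with group in the follow-up ANOVA and in the T2 part of the primary hypothesis.

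The offset is certain from the text; the bias is not. For an assumed linear change of 0 to 0.5 SD per six months it would be 0 to about 0.10 SD at T2, or 0 to about 0.05 SD on the T1/T2 mean, and it could act in either direction. That is modest beside the self-selection that the article acknowledges, but it is avoidable at little cost.

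**What to change.** - Set the control group's T2 at six months after T1, that is, T0 + 5 weeks + 6 months, to match the intervention group, and state this anchor in the design text.
- Record the actual date of every assessment.
- Keep any controls already assessed at six months after T0 in the main analysis, flag them, and report a T2 sensitivity analysis without them. Dropping them outright would remove a subset of a small group (49 required) defined by when they enrolled.

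Cost: the questionnaire is web-based, so the link is simply sent five weeks later and no clinic visit is added. The last control assessment moves by five weeks. Under the article's own rule for important modifications (Methods), the change has to be reported to the sponsor and the ethics committee and the registration updated. The required sample size does not change.

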**Primary outcome**			
PASC (PCS Score)	X	X	X
**Secondary outcomes**			
Somatic, Depression, and Anxiety symptoms (PHQ-15; PHQ-9; GAD–7)	X	X	X
Sleep (ISI)	X	X	X
Fatigue (FSS)	X	X	X
Post-exertional malaise (PEM)	X	X	X
Social support (ESSI)	X	X	X
Sense of coherence (SOC-3)	X	X	X
Distress (PSS-4)	X	X	X
Somatic symptom disorder (SSD-12)	X	X	X
Patients’ competence to cope with illness (PUK-2)	X	X	X
Quality of life (SF-36)	X	X	X
Satisfaction with treatment			X*
